### Sample size

Based on the existing research on the effectiveness of psychosocial interventions in children with mild ID and behavioural problems, the expectation is to find a small to medium effect on perceived competence [18]. A power analysis (two-tailed, alpha .05, statistic power 0.80) with two groups showed that 54 participants are necessary to show a small to medium effect. This calculation is based on a univariate analysis of variance with a baseline assessment, an assessment after the program, and a follow-up assessment with two groups. To explore the interaction-effects, four groups are needed, as both groups will be split again (e.g., boys versus girls) into both control group and experimental group. A power analysis (two-tailed, alpha .05, statistic power 0.80) with four groups showed that 80 participants are necessary to show a small to medium effect [19]. To compensate for 10 % attrition, the sample size needs to be 90 participants (children and parents) at minimum.

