### Statistical analysis

The data from all participants in experimental and control groups will be analysed according to the intent-to-treat principle. Missing data will be estimated with multiple imputation. The effectiveness of the program will be analysed with a multi-level path analysis in Mplus to account for differences between and within locations. The experimental and control group will be compared at baseline, post-test and follow up. We will control for baseline differences between the experimental and control group in demographic variables (e.g., gender and cultural background). Interaction effects will be analysed, as various studies on other interventions reported that the effectiveness of these interventions varies with differences in these variables [33–35]. All interaction effects will be studied in an explorative way with 2x2 ANOVA’s, with the experimental and control group each comprising two levels.

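### The 80 participants said to give 80% power for interactions do not size the planned 2x2 ANOVA, and the effect behind 54 and 80 exceeds a conventional medium group difference unless the correlation between assessments is high

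*Protocol article*

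**What the plan says.** The Sample size section takes its target from earlier research: "the expectation is to find a small to medium effect on perceived competence". With a two-sided alpha of 0.05 and power of 0.80, it reports that a power analysis "with two groups showed that 54 participants are necessary to show a small to medium effect". The basis is described as a "univariate analysis of variance with a baseline assessment, an assessment after the program, and a follow-up assessment with two groups".

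A second calculation sets the final size. "To explore the interaction-effects, four groups are needed, as both groups will be split again (e.g., boys versus girls", and a power analysis with the same alpha and power "with four groups showed that 80 participants are necessary to show a small to medium effect". Allowing for 10% attrition, the section arrives at a minimum of 90.

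The section gives no number for the effect, no metric, no correlation between assessments and no tested term. Under Statistical analysis, effectiveness is to be tested with a multi-level path analysis. For the moderators: "All interaction effects will be studied in an explorative way with 2x2 ANOVA’s, with the experimental and control group each comprising two levels".

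**The concern.** Fifty-four participants in two groups is few for an effect between small and medium. A plain two-group ANOVA with f = 0.175 would need 260. So it matters which test and which scale produced the 54, and what difference between the groups it stands for.

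The four-group figure raises a separate question. It is said to serve the exploration of interactions, and those are to be tested in 2x2 ANOVAs. If 80 comes from a different test, the stated power does not belong to the planned analysis.

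Readers will use the power statement to interpret a null result. If the detectable difference is larger than the label suggests, a null result could be misread as ruling out a modest benefit, or as showing that the effect does not vary between subgroups.

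**Working it through.** **Inputs.** From the Sample size section: two-sided alpha 0.05, power 0.80, three assessments, two or four groups, 10% attrition. Assumed because not stated: f = 0.175 (midway between the conventional small 0.10 and medium 0.25), correlation rho = 0.5 between assessments, sphericity, equal groups.

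**Step 1: reproduce the plan's figures.** For the group-by-time term with k groups and m = 3 assessments:

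- noncentrality = f² × N × m / (1 − rho)
- df1 = (k − 1)(m − 1), df2 = (N − k)(m − 1)

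Results:

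- Two groups, N = 54: 0.175² × 54 × 3 / 0.5 = 9.92; df 2 and 104; power 0.800. N = 53 gives 0.792, so 54 is the exact minimum.
- Four groups, N = 80: 0.175² × 80 × 3 / 0.5 = 14.7; df 6 and 152; power 0.816. N = 76 gives 0.791, so 80 is the smallest size with four equal groups.
- Attrition: 80 / 0.9 = 88.9, so 89, or 90 as an even number.

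One set of inputs returns every figure. Other readings at f = 0.175 do not: one-way ANOVA needs 260 (two groups) or 360 (four groups), and the between-subject effect in a repeated-measures ANOVA needs 174 or 244.

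**Step 2: does 80 size the planned interaction?** The test in Step 1 has 6 df and asks whether any of the four groups changes differently from the others. The 2x2 interaction of condition by moderator has 1 df. For one measurement and N = 80 (20 per cell), noncentrality = f² × 80, with df 1 and 76:

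| f | noncentrality | power |
|---|---|---|
| 0.10 | 0.80 | 0.14 |
| 0.175 | 2.45 | 0.34 |
| 0.25 | 5.00 | 0.60 |
| 0.317 | 8.05 | 0.80 |

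If the effects in the two subgroups differ by D (in SD units), each cell's interaction effect is ±D/4, so D = 4f. The detectable D is 4 × 0.317 = 1.27 SD. With adjustment for baseline it is about 1.10 SD at a baseline-to-outcome correlation of 0.5 and 0.91 SD at 0.7. For f = 0.175 the interaction would need about 260 participants.

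**Step 3: what is f = 0.175 as a group difference?** Suppose no difference at baseline and a difference d at both post-test and follow-up. Each group's deviation from the mean course is half the difference: 0, d/2, d/2. Removing its average, d/3, leaves −d/3, d/6, d/6. The mean square is (4 + 1 + 1)d²/36 / 3 = d²/18, so f = d/√18 = 0.236d. Then f = 0.175 means d = 0.175 / 0.236 = 0.74 SD. A conventional medium difference is 0.5 SD.

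The detectable d (80% power, sustained difference) depends on the correlation:

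| rho | N = 54 | N = 80 |
|---|---|---|
| 0.3 | 0.88 | 0.72 |
| 0.5 | 0.74 | 0.61 |
| 0.7 | 0.58 | 0.47 |
| 0.8 | 0.47 | 0.38 |

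At rho = 0.5, power for a full medium difference of 0.5 SD is 0.45 with 54 and 0.62 with 80. With 80 it is 0.85 at rho = 0.7. None of these figures allows for clustering.

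**The case against.** A reader might infer that the 80% power statement is simply false. The document does not support that. Cohen's f is the usual metric for an analysis of variance, 0.175 lies midway between small and medium on it, and both sizes then follow exactly. No figure in the section is miscalculated.

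A reader might also conclude that the trial has only a one-in-four to one-in-three chance of detecting its own target. That requires a target of 0.35 SD, which the article never states; the source of the expected effect is cited but not quantified. Nor is 0.74 SD a fixed property of the design. It depends on an unstated correlation and pattern over time, and it belongs to 54 children, whereas 80 evaluable children are planned. At correlations of 0.7 or more, those 80 detect a difference just under a conventional medium one or smaller. This objection stands and limits the second part of the point.

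On interactions, the article calls them exploratory, and on the same f scale the condition-by-moderator-by-time term (2 df) has about 94% power at f = 0.175. To say that 80 cannot power any interaction would therefore go too far. But that term still detects only a difference of about 1.21 SD between subgroup effects, and it is not the 2x2 ANOVA that the article plans. Calling the analyses exploratory does not remove the 80% power attached to them.

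A condensed article may leave f and the correlation to the full protocol. The point does not rest on their absence. It rests on a power claim that is made in print and does not match the planned test.

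**Conclusion.** The point holds in two parts. The firmer one is the interaction claim: 80 reproduces as a 6-df four-group-by-time test, while the planned 2x2 interaction has about 14%, 34% and 60% power at f = 0.10, 0.175 and 0.25. Those powers assume equal cells, a single measurement and no baseline adjustment; they do not depend on the correlation between assessments or on translating f into SD units. Even with baseline adjustment, only subgroup differences of roughly 0.9 to 1.1 SD are detectable.

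The second part is one of labelling. At the correlation that reproduces the plan's own figures, the effect behind 54 is about 0.74 SD, so the description misleads anyone who thinks in standardised differences. For the planned 80 evaluable children the detectable difference runs from about 0.72 to 0.38 SD over correlations of 0.3 to 0.8. This rests on inferred inputs and a sustained difference; that one set of inputs returns both 54 and 80 makes the inference strong but not certain.

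**What to change.** Keep the enrolment target of 90. In the Sample size section:

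- state f, the assumed correlation and the tested term;
- give the detectable two-group difference in SD units for 80 evaluable children as a range over the correlation (about 0.72, 0.61, 0.47 and 0.38 SD at 0.3, 0.5, 0.7 and 0.8), noting that it is before any allowance for clustering;
- withdraw the claim of 80% power for interactions and say that only subgroup differences of about 1 SD or more are detectable.

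The cost is wording only, with no extra participants. The downside is that the stated power becomes less favourable.

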### Intervention group

The intervention group will receive the program ‘You are okay’, in addition to care as usual. The program includes a support group for children and an online educational program for parents. The support group will consist of ten weekly sessions of 1.5 h with a booster session after six weeks. Each session will have the same structure but different themes. Each session will start with a warming up exercise. After this introduction, previous week’s experiences and homework assignments will be discussed. The program will continue with exercises, including role playing games, psycho-education, videos and practising coping and social skills. At the end of each session, the session will be summarized and the homework assessment will be explained. The themes of the sessions are shown in Additional file 2, and they are linked to the theoretical model explained in Fig. 1. Two therapists who work with children with mild ID will lead the support group. The therapists will be trained to ensure that they are familiar with the program materials and that they understand the theoretical model underlying the support group. The therapists will evaluate the program and each session individually. They will also exchange their experiences during intervision meetings.

In parallel to the support group for children, parents will be offered an online educational program. Parents will receive information on five themes, reflect on their role as a parent, and learn about the possible influence of their problems on their child. The five themes are shown in Additional file 2, and they are linked to the theoretical model described in Fig. 1. Parents will complete the educational program online at home. If necessary, a social worker who is involved in the family system, will visit them three times at home to complete the educational program. The social workers are trained in using the online educational program to support parents.

### Care as usual

Children in the control group will receive care as usual from the specialised institutes for children with mild ID and behavioural problems. These institutes formulate personal treatment goals for children in a so called “individual treatment program” (for instance, a goal could be to improve the interaction with peers or to learn to cope with feelings of anger without using verbal or physical aggression). A multidisciplinary team is always involved in the treatment program of each child.

### Assessments

Instruments will be adjusted to help children with mild ID complete the assessments, with the use of colours and emoticons corresponding the response options. According to the pilot study, the assessments are appropriate for children with mild ID.

The primary outcome will be children’s perceived competence, which consists of global self-worth, social acceptance, and COPMI-specific cognitions. It will be measured using the Dutch version of the Self Perception Profile for Adolescents (SPPA) [20, 21]. Children will complete two subscales: global self-worth and social acceptance. Each subscale contains five items measured on a four-point Likert scales. Different colours will be used to underline the response options. The reliability of this instrument is sufficient [20]. This instrument has been widely used by researchers in the field of intellectual disabilities [22].

Children’s perceived competence will also be measured using a short questionnaire on COPMI-specific cognitions developed by Van Santvoort [11]. The scale assesses whether a child experiences guilt, shame, and loneliness in relation to his/her parent with a mental illness. It contains three items measured on a five-point Likert scale, which together measure the COPMI-specific cognitions. The written response options are accompanied by emoticons. According to the study by Van Santvoort [11], these three items were moderate to highly correlated with each other.

Secondary outcomes will be children and parents’ perceived social support, perceived parental competence, parental involvement with their child’s treatment, positive parenting behaviour and children’s emotional and behavioural problems.

Children and parents’ social support will be assessed using a Dutch version of the Network of Relationships Inventory – Behavioural System Version (NRI-BSV) [23]. Children and parents will complete three of the eight subscales: ‘seeks safe haven’, ‘seeks secure base’ and ‘companionship’. Each subscale originally contained three questions measured on a five-point Likert scale. In the version designed for children, the five-point Likert scale was changed to a three-point Likert scale supported by colours, following the results from the pilot study. The reliability of this instrument was proven to be sufficient [23]. Parents’ social support will also be measured using the NRI-BSV and a short version of the Dutch questionnaire Social support list-interactions (SSL-12-I) [24]. It contains 12 items measured on a four-point Likert scale, and it measures the level of social support using three subscales: everyday support, support in problem situations and esteem support. The NRI-BSV is proven to be a valid instrument [24].

Two subscales, a competence scale and an incompetence scale, taken from different questionnaires will measure parental competence. The competence will be measured using the Parenting Self-Agency Measures [25]. It contains five items measured on a six-point Likert scale and assesses the perceived efficiency as a parent. The incompetence scale will be measured using a short version of the Dutch questionnaire ‘Nijmeegse ouderlijke stress index (Nijmegen parental stress index)’ [26]. It contains six items measured on a six-point Likert scale and assesses feelings of inadequacy as a parent. Both subscales have sufficient reliabilities [26, 27].

Parental involvement with their child’s treatment will be measured using a single question measured with a scale from 0 to 10 developed for the purpose of this study. It measures the degree of involvement of the parents in the treatment of the child.

Positive parenting behaviour will be measured using the Parenting Scale [27], which has been tested and appears to be a valid and reliable instrument. Parents will complete subscales laxness and over reactivity measured by 21 items on a seven-point Likert scale.

Children’s emotional and behavioural problems will be assessed using the Strengths and Difficulties Questionnaire (SDQ) [28, 29]. Children, parents and social workers will be asked to complete this 25-item questionnaire measured on three-point Likert scales. The questionnaire for children will include colour coded response options. This instrument assesses the strengths and difficulties of children in five domains: emotional symptoms, conduct problems, hyperactivity-inattention, peer problems and prosocial behaviour. Its reliability and validity is well established [30].

The following questionnaires will be used to study interaction effects. The severity of the parents mental illnesses will be measured using the Brief Symptom Inventory (BSI) [31] and parents’ well-being will be measured using the WHO-Five Well-being Index (WHO-5) [32]. The treatment coordinators of the children will provide background information to study other interaction effects (gender, age, country of birth, IQ, diagnoses of the child, type of treatment).

### Statistical analysis

The data from all participants in experimental and control groups will be analysed according to the intent-to-treat principle. Missing data will be estimated with multiple imputation. The effectiveness of the program will be analysed with a multi-level path analysis in Mplus to account for differences between and within locations. The experimental and control group will be compared at baseline, post-test and follow up. We will control for baseline differences between the experimental and control group in demographic variables (e.g., gender and cultural background). Interaction effects will be analysed, as various studies on other interventions reported that the effectiveness of these interventions varies with differences in these variables [33–35]. All interaction effects will be studied in an explorative way with 2x2 ANOVA’s, with the experimental and control group each comprising two levels.

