### Participants

Participants will be 10–20 year old children being treated for mild ID and behavioural problems at specialised institutes in the Netherlands and their parents with a mental illness. This age group is chosen because it corresponds with the age of the children in these institutes. The participating institutes specialise in treating children with mild ID and behavioural problems and offer children both residential care and part time treatment, depending on the severity of the problems of the children and their families. The researchers asked the institutes to participate in this study because of their population of children with mild ID.

The selected children had to have reached some stability in their lives in order to be able to reflect on their parent’s mental illness. Hence, the children who have been treated for at least three months, have not been in a crisis, and have been stable enough to handle potential emotional responses to the program, as indicated by the treatment coordinator, will be included in the study. Children who are not able to participate in a support group because of, for example, severe emotional or behavioural problems, will be excluded. In addition, children will be excluded if parents do not give consent, e.g., parents disagree with the child discussing the parent’s illness with others.

Many different support groups for different age groups of COPMI with average intelligence have been developed all based on the same principles. In the program ‘You are okay’, the experimental groups will formed according to children’s age; thus, age-groups will be formed. In the support group manual, different methods of the same exercises are described to match the needs of the specific age groups.

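### The multilevel analysis clusters by location only, although correlation from the support groups arises in the intervention arm alone; on the plain reading the standard error of the programme effect is too small

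*Protocol article*

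**What the plan says.** The Statistical analysis section names one clustering unit. Effectiveness is to be "analysed with a multi-level path analysis in Mplus to account for differences between and within locations". It mentions neither support group nor therapist pair as a level, and does not say whether the programme effect may differ by location.

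Other sections describe how treatment reaches the children:

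- **Participants:** the experimental groups follow age ("thus, age-groups will be formed").
- **Intervention group:** ten weekly sessions and a booster are held in a group. "Two therapists who work with children with mild ID will lead the support group".
- **Care as usual:** control children follow individual treatment programmes and attend no such groups.
- **Allocation:** children are matched on age, gender, type of setting and location, so both conditions occur within a location, and support groups are started within locations.

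The Sample size section makes no allowance for clustering: "This calculation is based on a univariate analysis of variance with a baseline assessment" and two later assessments in two groups. It gives two requirements. The first is "A power analysis (two-tailed, alpha .05, statistic power 0.80) with two groups showed that 54 participants are necessary". The second, for interaction effects, is a calculation "with four groups showed that 80 participants are necessary to show a small to medium effect", raised to 90 for 10% attrition.

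**The concern.** Children who share sessions, peers and therapists for ten weeks may end up more alike than children who do not. The programme works through peer exchange, and the primary outcome includes social acceptance and feelings of guilt, shame and loneliness, so some positive correlation within a support group is plausible.

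A location effect raises or lowers treated and control children together and largely cancels from their difference. A support-group effect falls on treated children only and does not cancel. A model that knows only locations therefore counts the treated children at a location as more independent than they are, and the p-value for the programme effect comes out too small. The Discussion makes demonstrated effectiveness the condition for regular implementation, so a false positive would have practical consequences.

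**Working it through.** **1. Inputs.** From the Sample size section: two-sided alpha 0.05, power 0.80, three assessments, totals of 54 and 80, and 10% attrition. The effect is described only in words ("the expectation is to find a small to medium effect on perceived competence"). Not given, and therefore assumed: Cohen's f = 0.175 (the midpoint of 0.10 and 0.25), correlation between assessments 0.5, 6 or 8 children per support group, ICC 0.01 to 0.20, equal arms.

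**2. Reproducing the stated totals.** For the group-by-time test with k groups and three assessments, the noncentrality is N × 3 × f² / (1 − 0.5), with (k − 1) × 2 and (N − k) × 2 degrees of freedom.

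- k = 2, N = 54: 54 × 3 × 0.030625 / 0.5 = 9.92; df 2 and 104; power 0.800.
- k = 4, N = 80: 80 × 3 × 0.030625 / 0.5 = 14.70; df 6 and 152; power 0.816. With 76, the next smaller equal-group total, power is 0.791.
- 80 / 0.9 = 88.9, stated as 90.

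Both totals are reproduced with independent participants, so neither contains a design effect.

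**3. Effect of support groups in one arm.** With m children per group, the intervention-arm design effect is DE = 1 + (m − 1) × ICC. With equal arms the variance ratio of the difference is (1 + DE)/2 and the SE ratio is its square root. If groups are ignored, the type I error is 2 × [1 − Φ(1.96 / SE ratio)]. The last two columns give two-group power for an analysis with the correct standard error: the noncentrality of step 2 divided by the variance ratio. They are approximate and precede any small-sample correction.

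| m | ICC | DE | Variance ratio | SE ratio | Type I if ignored | Power, N = 54 | Power, N = 80 |
|---|---|---|---|---|---|---|---|
| 6 | 0.01 | 1.05 | 1.025 | 1.012 | 0.053 | 0.79 | 0.93 |
| 6 | 0.05 | 1.25 | 1.125 | 1.061 | 0.065 | 0.75 | 0.90 |
| 8 | 0.05 | 1.35 | 1.175 | 1.084 | 0.071 | 0.73 | 0.89 |
| 6 | 0.10 | 1.50 | 1.250 | 1.118 | 0.080 | 0.70 | 0.87 |
| 8 | 0.10 | 1.70 | 1.350 | 1.162 | 0.092 | 0.66 | 0.84 |
| 6 | 0.20 | 2.00 | 1.500 | 1.225 | 0.110 | 0.62 | 0.80 |
| 8 | 0.20 | 2.40 | 1.700 | 1.304 | 0.133 | 0.56 | 0.74 |

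Without clustering, two-group power at N = 80 is about 0.94. Scaling 54 by the variance ratio gives 54 × 1.125 ≈ 61 to 54 × 1.35 ≈ 73 over ICC 0.05 to 0.10, still below 80.

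**4. Does a location intercept absorb it?** Simulation, 20,000 runs per setting, both arms in every location, location ICC 0.05, group effects in the intervention arm only, 6 children per group:

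| Layout | Group ICC 0 | 0.05 | 0.10 | 0.20 |
|---|---|---|---|---|
| 8 locations, one group each | 0.051 | 0.067 | 0.087 | 0.121 |
| 4 locations, two groups each | 0.050 | 0.064 | 0.087 | 0.122 |

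The entries are type I errors of the location-intercept analysis. With 8 locations and ICC 0.10 the model SE averaged 0.196 against a true SD of 0.223. So the intercept does not absorb the correlation even when each location has exactly one support group.

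**5. Programme effect allowed to vary by location.** Type I error was about 0.05 with a t reference on the number of locations minus 1, but 0.09 to 0.19 with a normal reference and 3 to 8 locations.

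**The case against.** The best defence is that one sentence in an article does not fix the model. Support groups sit within locations, so a multilevel model whose programme effect varies by location, or a location-robust variance, would pick up the support-group correlation. Random-effects structure and degrees of freedom are details an article commonly leaves to the full plan, which is not shown. A reader might infer that the standard error is certainly wrong; the document does not support that, because the result depends on location entering as an intercept only. What remains is that the article does name the level it accounts for, that level is not where the treatment-related correlation arises, and neither alternative is stated. Step 5 shows that a varying effect helps only with a suitable reference distribution.

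The second defence is that the size is assumed. This stands. The one remark about small groups, in the Background, describes existing programmes for children of average intelligence, and the text never says that several groups run at one location.

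A reader might also apply the inflation to the nominal 80% and infer that power for the programme effect falls to 67 to 75%. The document does not support this. The 80 serves the four-group interaction tests, which the Statistical analysis section calls exploratory; the two-group comparison was sized at 54. With 80 analysable children it has room to spare.

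Finally, with few support groups their variance will be poorly estimated. That is a real cost of the remedy, but not a reason to set the variance to zero.

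**Conclusion.** The concern holds in conditional form. The only stated clustering level does not capture dependence that exists in one arm, and under a location intercept the standard error of the programme effect is too small for any positive within-group ICC. With 6 to 8 children per group, ICC 0.05 to 0.10 and equal arms, all assumed, the true standard error is about 6 to 16% larger and type I error is about 6.5 to 9%. At ICC 0.20 type I error is 11 to 13%; at ICC 0.01 the matter is negligible.

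Power for the programme effect is a lesser issue. Under the inferred f and correlation, it falls from about 0.94 to 0.84 to 0.90 at 80 analysable children over the main range, before small-sample degrees of freedom. The 54 figure is the one that no longer delivers 80%, giving about 0.66 to 0.75. This should be settled before analysis, but it does not undermine the design.

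**What to change.** - Record a support-group identifier for every intervention child during delivery.
- Specify a partially nested model: a random support-group effect in the intervention arm only, with each control child as a singleton. Keep location as a fixed or random effect, and use small-sample degrees of freedom.
- If a programme effect varying by location is preferred, say so and state a t reference on the number of locations minus 1.
- In the Sample size section, state that 54 and 80 assume independent participants, and give the group size and ICC used for any allowance.

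The cost is one extra variable, a few sentences and somewhat wider intervals. With 90/2 = 45 treated children and 6 to 8 per group there would be only about 6 to 8 groups, so their variance will be imprecise and the small-sample correction matters.

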### Allocation

Using a quasi-experimental design, each child and his or her parent will be assigned to a condition (experimental group or control group) based on matching. Because in practice it is not possible and appropriate to form support groups with children of different ages and from different locations, matching based on age, gender, type of setting (residential or part-time) and location will be used. Therefore, it will be possible to start support groups in different locations with children of different age groups and an equal distribution of both genders and type of treatment. An independent researcher will perform the allocation before baseline assessment takes place and will assure that the experimental and control group will match.

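### In a non-randomised comparison, the only stated adjustment is for demographic differences; the prognostic measures the trial collects are given no covariate role in the main model

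*Protocol article*

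**What the plan says.** All references are to the protocol article.

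- **Allocation.** The design is quasi-experimental: "each child and his or her parent will be assigned to a condition (experimental group or control group) based on matching". The factors are few: "matching based on age, gender, type of setting (residential or part-time) and location will be used". The reason given is practical, namely the need to form support groups by age and place. On timing: "An independent researcher will perform the allocation before baseline assessment takes place".
- **Statistical analysis.** The main model: "The effectiveness of the program will be analysed with a multi-level path analysis in Mplus to account for differences between and within locations". The waves: "The experimental and control group will be compared at baseline, post-test and follow up". The adjustment: "We will control for baseline differences between the experimental and control group in demographic variables (e.g., gender and cultural background". Interaction effects are exploratory 2x2 ANOVAs.
- **Assessments.** "The severity of the parents mental illnesses will be measured using the Brief Symptom Inventory". That instrument, the WHO-5, and the background data from treatment coordinators (including IQ and the child's diagnoses) are introduced for studying interaction effects. The SDQ appears as a secondary outcome.
- **Background.** The main risk factors listed are the child's mild ID and behavioural problems, and the parent's mental illness and mild ID.
- **Participants.** Residential or part-time care depends on how severe the child's and family's problems are. The caregiver who takes part may be the parent without the illness, a foster parent or a stepparent.

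**The concern.** In a randomised trial a thin covariate list mainly costs precision. Here no random element is described, so a prognostic difference between the groups that is neither matched nor adjusted for passes into the effect estimate, and recruiting more children does not remove it.

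The factors that the article's own theory ranks highest are the ones the adjustment sentence does not reach. Its wording also leaves open that covariates will be picked after looking at which baseline variables differ. That would make the model depend on the data, and a difference large enough to matter can go unflagged in a sample of this size.

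The Discussion says the program would be eligible for routine use once effectiveness is shown, and the limitations listed do not mention confounding.

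**Working it through.** **1. Which variables are protected, and how.**

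| Baseline variable | Matched | Named for adjustment | Other stated use |
|---|---|---|---|
| Age | yes | no | interaction |
| Gender | yes | yes (example) | interaction |
| Setting / type of treatment | yes | no | interaction |
| Location | yes | no | level of the multi-level model |
| Cultural background | no | yes (example) | country of birth: interaction |
| Parental severity (BSI) | no | no | interaction |
| IQ, child's diagnoses | no | no | interaction |
| SDQ | no | no | secondary outcome |
| Perceived competence | no | not stated | one of three waves compared |

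Allocation precedes the baseline assessment, so baseline scores on perceived competence, SDQ and BSI cannot be matched on.

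**2. Does the plan use the baseline outcome?** The Sample size section says, for the comparison of the two conditions: "This calculation is based on a univariate analysis of variance with a baseline assessment, an assessment after the program, and a follow-up assessment with two" (cut before its last word). It gives no numerical effect size or correlation between waves. Assume f = 0.175 (midpoint of 0.10 and 0.25), rho = 0.5, m = 3 waves, alpha 0.05, and a group-by-time test with lambda = f²·N·m/(1 − rho), df1 = (k − 1)(m − 1), df2 = (N − k)(m − 1):

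- k = 2, N = 54: lambda = 0.030625 × 54 × 3 / 0.5 = 9.92, df 2 and 104, power 0.800. The stated 54 is reproduced.
- k = 4, N = 80: lambda = 0.030625 × 80 × 3 / 0.5 = 14.70, df 6 and 152, power 0.816. The stated 80 is reproduced.
- Attrition: 80 / 0.90 = 88.9, so 89 against the stated 90.

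With the same f and rho, a between-groups test needs 174 and 244, and a time main effect needs 54 and 56. Of these three variants, only group-by-time gives both stated figures. The inputs are assumed, so this supports the article's own statement that baseline is in the calculation; it does not prove the form of the final model.

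**3. How large could residual confounding be?** The document gives neither an imbalance nor a correlation, so both are assumed. For a standardised covariate with a linear effect, and nothing else absorbing it, bias = imbalance × correlation with the outcome.

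- 0.3 × 0.4 = 0.12 SD. Against d = 2f = 0.35 this is 0.12 / 0.35 = 34%.
- Range: 0.1 × 0.3 = 0.03 SD (9% of 0.35) up to 0.3 × 0.7 = 0.21 SD (60%).

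This applies to a comparison of levels. If the model already uses the baseline outcome, the correlation must be read as the association that remains after that, which could be smaller.

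**4. Would a look at baseline differences catch it?** With 40 per group the standard error of a baseline difference is sqrt(2/40) = 0.224 SD. An imbalance of 0.3 SD is 0.3 / 0.224 = 1.34 standard errors, below 1.96, so a conventional test would not flag it.

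**The case against.** **Condensed article.** A full covariate list is commonly left to an analysis plan, which is not shown, and the examples given are only illustrative. This stands as far as missing detail goes. But the article does state a rule, and it limits the named control to demographic variables while giving the prognostic measures another purpose. That rule is weak for a quasi-experiment.

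**Matching limits confounding.** Allocation is by an independent researcher after consent, no self-selection into a condition is described, and setting reflects severity in part. This stands. It is why confounding can be called possible but not shown. Setting is two categories, however, and does not replace graded measures of IQ, behaviour or parental symptoms.

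**No selection rule is stated.** True: the sentence can also mean adjusting for demographics in general. Data-driven choice is one reading of loose wording, not a stated procedure.

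**A stronger reading that fails.** A reader might infer that the baseline outcome is left out of the analysis and power is lost. At 40 per group and d = 0.35, an unadjusted post-test comparison has power 0.34, against 0.43 or 0.58 after adjusting for a baseline correlated 0.5 or 0.7. But no section plans a post-test-only comparison. The groups are compared at all three waves, and the sample size calculation includes baseline. The adjustment sentence does not say that demographics are the whole model. What is missing is how baseline enters the path model.

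**The remedy is not automatic.** BSI may describe a caregiver other than the ill parent, and the SDQ has three informants. This stands and is dealt with in the fix.

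**Conclusion.** The point holds in a limited form. The stated adjustment covers demographic differences only, with one of its two examples already matched. BSI, IQ and diagnoses are directed to exploratory interactions, baseline SDQ has no covariate role, and none of them is a matching factor.

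Residual confounding is possible. Its direction is unknown, and 0.12 SD is an illustration resting on two assumed inputs, not an estimate for this trial. The role of the baseline outcome needs to be stated, but neither its omission nor a loss of power is shown. The rule should be changed before the data are analysed, because the measures are already planned and the weakness cannot be repaired by sample size.

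**What to change.** In the Statistical analysis section, replace control for baseline differences in demographic variables with an adjustment set fixed in advance and used whatever imbalance is observed:

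- the baseline value of the outcome analysed, stating how it enters the path model;
- the matching factors: age, gender and setting, with location as the model level or as a factor;
- a short prognostic list: baseline SDQ total from one named informant, IQ, and BSI of a defined parent.

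State whose BSI score is used when both parents take part, and give a rule for when the participating caregiver is not the parent with the mental illness. One option is to treat that score as missing in the multiple imputation already planned. Cultural background can stay if wanted. The exploratory interaction analyses can remain as they are.

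**Cost.** This is a change of wording, and the measures are already in the assessment plan. If each covariate takes one parameter and location is the model level, the set uses seven degrees of freedom (baseline outcome, age, gender, setting, SDQ, IQ, BSI) in about 80 to 90 children. It uses six when the outcome is the same SDQ total, and more if location is a fixed factor. The list should therefore stay short.
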